### Data management {19}

The REDcap software, with a two-stage verification login, will also be used for safe data management (project-redcap.org; redcap.vanderbilt.edu). The data will be pseudonymized and all participants will have a specific code. Access to decrypted data and safekeeping of the decryption key will be limited to the principal investigator and the study nurse. The principal investigator is responsible for communicating important protocol modifications and is together with the research nurse responsible for encrypting participant data and protecting the decryption key.

### Confidentiality {27}

All data managements and analysis are done using unidentified data. The participating spine surgeons will only have access to data generated on their own site and cannot see the other recruiting centers.

### Plans for collection, laboratory evaluation, and storage of biological specimens for genetic or molecular analysis in this trial/future use {33}

No laboratory test or biological materials are collected during this trial.

## Statistical methods

### Statistical methods for primary and secondary outcomes {20a}

All endpoints will be analyzed in the modified intention to treat (mITT) population, defined as randomized patients who are still alive without having emigrated or left the study after 2 and 5 years.

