### Trial design {8}

The MyRanc study is a multicenter randomized, controlled, parallel-group non-inferiority trial with 300 adult patients allocated in a ratio of 1:1 to two treatment groups: posterior muscle-preserving selective laminectomy (L-group) and laminectomy with instrumented fusion (LF-group).

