### Outcomes {12}

The primary endpoint is reoperation for any reason at 5 years of follow-up. Reoperation will be considered in case of:Postoperative hematoma or reperfusion injury with neurologic deterioration within hours/days after the primary surgeryChange in sagittal alignment (kyphosis, DJK of more than 40 mm cSVA [9] and/or C2–C7 Cobb < −10°) with corresponding symptoms of camptocormia/increased pain/neurological deteriorationASP defined as degenerative changes on an adjacent level diagnosed with MRI and concomitant symptoms of myelopathy and/or radiculopathyImplant failure (clear radiolucency around >1 screw or rod breakage with increased neck pain and/or neurologic deterioration)Postoperative infection that requires revision surgery

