### Sample size {14}

Based on data from the national Swedish spine registry on patients with CSM, reoperation was estimated to be 3.5% after stand-alone laminectomy and 7.4% after laminectomy and fusion. Five-year mortality was estimated to be 16.3% in the same population [31].

We further determined that excluding a 5% excess rate of reoperation in the laminectomy group vs laminectomy and fusion was a clinically relevant target for the study and therefore set the non-inferiority margin at 5 percentage points (pp).

With a planned sample size of 300 participants and with regard to mortality and an additional 5% loss due to dropout and emigration, we end up with 236 analyzable patients. This results in a power of 86% based on simulation using rerandomization. The reason for stopping at 300 patients was made on the calculation on how many patients it is reasonable for the four sites to include in 4–5 years. Ideally, we would have reached for 90% power but have agreed to compromise with a power over 85% if that means that we will finish the study in due time.

All statistical analyses were performed in R [32], version 4.0.5 (R Foundation for Statistical Computing, Vienna, Austria), and the R code used in the sample size calculation may be received upon request.

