### Methods in analysis to handle protocol non-adherence and any statistical methods to handle missing data {20c}

Dropouts may be one out of two entities: (1) the participant actively leaves the study or (2) the participant has died or does not show up on follow-ups for unclear reasons. In case 1, the participant will not be part of the study anymore and data will not be retrieved from other information sources. In case 2, information about living participants will be retrieved from the medical records, radiographs, and the Swedish patient registry. In case 2, missing PROMs will be imputed using multiple imputation [44]. Reoperations, adverse events, and radiographs will not be imputed.

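### The primary analysis set keeps only patients alive and still in the study at 5 years, so observed reoperations are deleted, power is lost, and the non-inferiority test can be biased in a direction that the protocol does not fix

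*Protocol article*

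**What the plan says.** In the protocol article, *Outcomes {12}* states: "The primary endpoint is reoperation for any reason at 5 years of follow-up". The listed grounds for reoperation include early ones (haematoma within hours or days, infection needing revision) and late ones (adjacent segment pathology, change in alignment, implant failure).

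*Statistical methods for primary and secondary outcomes {20a}* places all endpoints in a modified intention-to-treat set, "defined as randomized patients who are still alive without having emigrated or left the study after 2 and 5 years". The Abstract repeats this.

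*Sample size {14}* builds the trial on that set. It takes the 300 randomised, a mortality figure ("Five-year mortality was estimated to be 16.3% in the same population") and "an additional 5% loss due to dropout and emigration, we end up with 236 analyzable patients", and reports 86% power.

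*Methods in analysis to handle protocol non-adherence {20c}* does not bring the lost events back. For those who withdraw: "In case 1, the participant will not be part of the study anymore and data will not be retrieved from other information sources". For those who die or stop attending, outside sources are searched only for the living, and reoperations are not imputed.

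Mortality at 5 years is listed as a secondary outcome in *Outcomes {12}*.

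**The concern.** Membership of the primary set depends on what happens in the 5 years after randomisation. A patient reoperated in the first week for a haematoma who dies in year 3 leaves both numerator and denominator, although the primary event is on record.

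Three things follow.

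- Observed events are discarded in a trial that expects few of them.
- The patients who remain are no longer a randomised comparison. The protocol describes an elderly, often frail population, and participants are not blinded. Links between arm, reoperation, death and withdrawal are plausible, and the claim of non-inferiority rests on this one comparison.
- The rule cannot be applied as written to 5-year mortality, because nobody in a set of 5-year survivors has died.

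**Working it through.** **Inputs from the protocol.** 300 patients, 1:1 (*Trial design {8}*). Reoperation 3.5% (laminectomy) and 7.4% (fusion), 5-year mortality 16.3%, further loss 5%, margin 5 percentage points (*Sample size {14}*). Two-sided 95% interval with its upper limit below the margin, i.e. one-sided 2.5% (*Statistical methods {20a}, Primary outcome*).

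**1. The plan's own figures.** Analysable: 300 × (1 − 0.163 − 0.05) = 236.1, matching 236, or 118 per arm. Excluded: 300 − 236 = 64 (21.3%).

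Power by normal approximation is Φ((0.05 + 0.039)/SE − 1.96), with SE = √[(0.035 × 0.965 + 0.074 × 0.926)/n]. At n = 118, SE = 0.02944 and power is 85.6%. A simulation of the planned permutation test (without blocking on sex) gives 85.0% at 118 and 86.0% at 119 per arm. The stated 86% reproduces.

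**2. Power with all randomised patients kept.**

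| n per arm | SE | Power |
|---|---|---|
| 118 | 0.02944 | 85.6% |
| 136 | 0.02743 | 90.1% |
| 150 | 0.02612 | 92.6% |

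The last row assumes that every reoperation precedes exit. If reoperations and losses are both spread evenly over 5 years, half of the events among lost patients are seen. The recorded rates are then multiplied by 1 − 0.213 × 0.5 = 0.8935, giving 3.13% and 6.61%, and power is 92.9%. The permutation test gives about 92% to 93% across this range.

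**3. Events deleted.** Expected reoperations in 300: 150 × (0.035 + 0.074) = 16.35. If all are early, 0.213 × 16.35 = 3.5 observed events are deleted. If events and losses are spread evenly, half of that, 1.7. The protocol does not give the timing, so the range is 1.7 to 3.5. The set itself is expected to contain 236 × 0.0545 = 12.9 events.

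**4. Effect on the error rate (assumed retention; the protocol gives none).** Put the truth at the margin: 12.4% after laminectomy and 7.4% after fusion. Let 78.7% of patients without reoperation be retained, and a fraction r of those with reoperation. The rate seen in an arm with true rate p is p·r / [p·r + (1 − p) × 0.787]. With r = 0.60:

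- laminectomy: 0.0744 / (0.0744 + 0.6894) = 9.74%
- fusion: 0.0444 / (0.0444 + 0.7288) = 5.74%

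The chance of a false non-inferiority claim is Φ((0.05 − d)/SE − 1.96), where d is the observed excess, SE is computed from the observed rates, and n = 118 per arm.

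| 60% retention of reoperated patients | Observed excess | SE | One-sided error |
|---|---|---|---|
| Neither arm (loss unrelated to reoperation) | 5.0 pp | 0.0387 | 2.5% |
| Both arms | 4.0 pp | 0.0347 | 4.7% |
| Laminectomy only | 2.3 pp | 0.0364 | 10.9% |
| Fusion only | 6.7 pp | 0.0371 | 0.8% |

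**The case against.** A reader might infer that the rule biases the test towards non-inferiority. The protocol does not support that. If loss is unrelated to reoperation there is no bias. If reoperated patients are lost mainly after fusion, the test becomes conservative. Nor does shrinkage of the difference always favour the claim. At the planning rates the true difference is −3.9 points, so shrinkage moves the estimate towards the margin. The anti-conservative result with equal loss in both arms arises when laminectomy is truly worse by about the margin. No passage says how often reoperated patients are lost, so 60% is only an illustration.

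A reader might also infer that the 86% is wrong, or that the choice of set is why the authors accepted it. Neither holds. The figure reproduces for the chosen set. The authors write "Ideally, we would have reached for 90% power but have agreed to compromise with a power over 85" per cent, and the reason they give is how many patients four sites can reasonably enrol in 4 to 5 years.

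Finally, one can say that restricting to 5-year survivors with complete follow-up gives a simple binary endpoint with known status. That is true, but it does not justify deleting events already observed, and a binary endpoint is available without it.

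What stands against all of this is the stated deletion rule, the power it costs, and an error rate in the deciding test that randomisation no longer protects.

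**Conclusion.** The point holds. By its own wording, the primary analysis set removes patients whose primary event has been observed, and no other section shown restores them or gives an all-randomised analysis. The expected exclusion of 64 patients and the power difference (about 86% against about 92% to 93%) follow from the protocol's planning figures. The 1.7 to 3.5 deleted events also depend on when reoperations and losses occur, which is assumed. Bias is possible, not shown: its size and direction depend on how loss relates to reoperation in each arm, and the protocol is silent on that. The mortality inconsistency needs no assumption.

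**What to change.** - Make all randomised patients, analysed as randomised, the primary analysis set. Count any reoperation recorded up to 5 years, death or exit as a binary outcome. The planned rerandomisation test and the 5-point margin then stand unchanged.
- As sensitivity analyses, report cumulative incidence with death as a competing event, and the present modified set. Making the competing-risk analysis primary is possible, but it would mean rewriting the planned test, and the defect does not require that.
- Analyse 5-year mortality in all randomised patients.
- Amend section {20c} so that reoperation data up to the date of death are retrieved for patients who die, and data collected before withdrawal are kept where consent allows. The consent text is not shown, so this needs checking.
- Restate the power for the new set.

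**Cost.** No extra recruitment. The medical records and patient registry are already named as sources, but the retrieval rules change, and under section {25} a protocol change must be resubmitted for ethical approval. The estimand becomes reoperation risk in the presence of death, and a patient who exits before 5 years counts as having no later reoperation. The sensitivity analyses are there to show how much that matters.

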#### Primary outcome

To test for non-inferiority, a two-sided 95% confidence interval (CI) for the difference in failure (reoperation) rates between the two groups will be computed. To account for the sparsity of events, the CI will be computed using rerandomization techniques [43], blocked on sex, since the randomization was stratified on sex. More precisely, a null distribution for the test statistic, i.e., the difference in failure rates, under the null hypothesis that the non-inferiority margin is correct will be generated via permutations. The one-sided *p*-value is the proportion of simulated test statistics that are larger than the observed one. To generate the null distribution, the non-inferiority margin of 0.05 will first be subtracted from the observed 0/1 failure variables in the non-fusion group. These modified outcomes will then be permuted a large number of times, recording the difference in means between the groups for each permutation. Non-inferiority will be claimed if the upper limit of the CI is less than 5 pp. If non-inferiority is demonstrated, superiority will also be tested using the same CI, although the study is likely underpowered to detect this.

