### Recruitment {15}

Patients with CSM are referred by a general practitioner to a consulting spine surgeon at a large center. Four large spine centers in Sweden are participating in the trial with patient enrolment to secure the reach of the target sample size. No specific strategy to promote the recruitment of patients is used.

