## Assignment of interventions: allocation

### Sequence generation {16a}

Participants will be allocated to either stand-alone laminectomy or laminectomy and fusion through randomization with a 1:1 ratio using the REDcap software (Research Electronic Data Capture), after informed consent and agreement to be included in the study. After inserting the patient’s personal number into REDcap, the program reports the random allocation of the patient according to the pre-constructed randomization list. The randomization is stratified for center and participant sex, i.e., using separate lists for each center and sex. The allocation sequence utilizes balanced blocks of three different sizes occurring in a random sequence. The principal investigator and study collaborators are blinded to the sequence, the block sizes, and the block sequence.

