#### Secondary outcomes

The secondary outcomes will be analyzed using ordinal regression models, adjusted for sex. In addition, each secondary endpoint will be dichotomized and analyzed using logistic regression. The dichotomization will be done by comparing baseline and follow-up data, either based on MCID when applicable or else by defining success as an improvement from baseline. All secondary endpoints will be analyzed at 1, 2, and 5 years of follow-up, but not until the study is closed.

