## Trial status

The trial started in February 2022 with four sites in Sweden, the Department of Surgical Sciences, the Academic University Hospital in Uppsala; the Department of Neurosurgery, Karolinska University Hospital in Stockholm; the Neuro-Orthopaedic Center, Ryhov Hospital in Jönköping; and the Department of Orthopaedics, Sahlgrenska University Hospital in Gothenburg. More sites may be recruited during the enrollment phase. The expected enrollment is 5 years, and the conclusion of the study is estimated at 10 years.

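### Randomisation is stratified by centre and sex, but no analysis uses centre: the primary test is blocked on sex only, for a reason that describes the design incompletely

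*Protocol article*

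**What the plan says.** Under Sequence generation {16a}, the protocol article states: "The randomization is stratified for center and participant sex, i.e., using separate lists for each center and sex". The same section adds: "The allocation sequence utilizes balanced blocks of three different sizes occurring in a random sequence". Recruitment {15} gives the number of sites: "Four large spine centers in Sweden are participating in the trial". Four centres and two sexes make 4 × 2 = 8 lists. Trial status leaves room for growth: "More sites may be recruited during the enrollment phase".

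Under Statistical methods {20a}, Primary outcome, the permutation test and its confidence interval are "blocked on sex, since the randomization was stratified on sex".

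Under Statistical methods {20a}, Secondary outcomes: "The secondary outcomes will be analyzed using ordinal regression models, adjusted for sex". The next sentence reads: "In addition, each secondary endpoint will be dichotomized and analyzed using logistic regression". It names no covariates. Nowhere does the article bring centre into an analysis or say why it is omitted.

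**The concern.** A rerandomisation test compares the observed result with results under allocations that the trial could have produced. The authors accept this principle, since they block on sex because sex was a stratification factor. They apply it to one of two factors. Permuting within sex alone admits reallocations with large imbalances inside a centre, which separate balanced lists per centre would prevent among randomised patients.

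The non-inferiority claim rests on the upper limit of this interval. If centre predicts reoperation and is ignored, the permutation distribution is somewhat too wide and the test loses some power. Centre is a plausible predictor: patients come through orthopaedic or neurosurgical departments in different hospitals, and the decision to reoperate involves judgement. The sponsor has already settled for 86% power instead of 90%, so an avoidable loss is worth removing.

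A separate statistical analysis plan may exist, but this is not an open detail left to it. The article fixes the blocking factor and gives a reason, and that reason omits half of the stratification.

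**Working it through.** **Inputs from the article.** Sample size {14}: "reoperation was estimated to be 3.5% after stand-alone laminectomy and 7.4% after laminectomy and fusion"; 300 patients; five-year mortality 16.3%; a further 5% loss; margin 5 percentage points; 236 analysable; power 86%. Statistical methods {20a}: two-sided 95% interval, so one-sided 0.025 at the upper limit.

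**Step 1: the plan's own figures.**
- Analysable patients: 300 × (1 − 0.163 − 0.05) = 236.1, or 118 per group.
- Standard error of the difference: √[(0.035 × 0.965 + 0.074 × 0.926)/118] = √(0.1023/118) = 0.0294.
- Power: Φ[(0.05 + 0.039)/0.0294 − 1.96] = 85.6%.

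Both stated figures reproduce.

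**Step 2: does the blocking factor matter?** The planned test was simulated: 0.05 subtracted from the outcomes in the laminectomy-alone group, then permutation within blocks, counting the tail that favours laminectomy alone. The article does not give everything needed, so these are assumptions:
- centre shares of 35/30/20/15%;
- block sizes 2, 4 and 6;
- a 2.7:1 male-to-female ratio, as in the Background;
- no effect of sex on reoperation;
- random loss of 64/300 = 21.3%.

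Each test used 800 permutations. There were 2,500 runs for power (3.5% v 7.4%) and 4,000 for type I error (12.4% v 7.4%, a true excess of 5 points).

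| Assumed spread of reoperation rates between centres | Power, sex only | Power, centre × sex | Type I, sex only | Type I, centre × sex |
|---|---|---|---|---|
| None | 85.0% | 84.7% | 2.7% | 2.8% |
| 4-fold | 86.3% | 86.3% | 2.7% | 2.8% |
| 16-fold | 84.8% | 87.0% | 2.5% | 2.6% |

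Monte Carlo standard errors are about 0.7 points for power, √(0.85 × 0.15/2500), and 0.25 points for type I error, √(0.025 × 0.975/4000).

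**Step 3: how extreme is the 16-fold case?** The relative rates were 0.25, 0.5, 1 and 4. Their weighted mean is 0.35 × 0.25 + 0.30 × 0.5 + 0.20 × 1 + 0.15 × 4 = 1.0375. Fusion-group rates then run from 7.4% × 0.25/1.0375 = 1.8% to 7.4% × 4/1.0375 = 28.5%. Only at that spread does centre blocking yield a visible gain, about 2 points.

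**Step 4: sparsity.** Expected reoperations: 118 × 0.035 + 118 × 0.074 = 4.1 + 8.7 = about 13. With a 2.7:1 ratio, 236/3.7 = about 64 analysable women, or 64/4 = 16 per centre on average. Expected events per female stratum average 13/(3.7 × 4) = 0.9. Small strata therefore need a rule.

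**The case against.** The strongest reply is that nothing of consequence is broken. The simulated error rate stays near nominal whichever blocking is used, and any effect of ignoring a prognostic centre is conservative. It does not help a false claim of non-inferiority. Common reoperation criteria are listed under Outcomes {12}, and adherence to them is monitored under {11c}, which should narrow differences between centres. All of this stands, and it limits the point to consistency and a little efficiency.

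A reader might infer that sex-only blocking makes the primary test invalid and that centre blocking would restore exact validity. The documents do not support that. Free permutation within centre-by-sex strata would still not reproduce the randomly sequenced blocks. Subtracting a constant 0.05 from 0/1 outcomes also makes the test approximate at the margin under any blocking.

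A reader might also infer that centre terms in the secondary models remove a share of outcome variance equal to the intraclass correlation, at no cost. That is linear-model reasoning. In ordinal and logistic models, a prognostic covariate moves the odds ratio from a marginal to a conditional one, further from the null, and generally increases its standard error. The article also gives no intraclass correlation. And there is a cost: three extra parameters with four sites, and a risk of separation where events are rare.

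What the reply does not answer is the text itself. The stated reason for the blocking describes the design incompletely, and no reason is given for dropping centre.

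**Conclusion.** The mismatch is explicit and should be corrected, as a low-cost improvement and not as a threat to the trial. Omitting centre does not inflate type I error. If centre predicts reoperation, the primary test is slightly conservative and gives up between nothing and about 2 points of power. That size depends on the assumed centre shares, block sizes and spread of rates, none of which the article gives. The sample size calculation is unaffected.

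For the secondary outcomes, the ordinal models omit one of the two stratification factors. For the logistic models the article states no adjustment at all, so it would be inaccurate to say that they adjust for sex. No numerical gain can be claimed for these models from the documents. The reason to include centre is agreement with the design.

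**What to change.** In Statistical methods {20a}, Primary outcome, permute within the centre-by-sex randomisation strata and give the reason as stratification on centre and sex. State before analysis how very small strata are merged and how sites added during enrolment are treated.

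In Secondary outcomes under the same heading, include centre and sex in both the ordinal and the logistic models. Pool small centres, or use a penalised or stratified method, where events are sparse, and report the odds ratios as conditional on these factors. If the sponsor prefers to omit centre, the article should justify that and still correct the sentence on stratification.

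The cost is a few lines of text and code, no parameters in the permutation test, and one parameter per centre beyond the first in the regression models. The article defers analysis until the trial is closed, so the change can be made before any outcome data are analysed.
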